### Randomization and blinding

2.5

Participants will be randomized 1:1 to taVNS group or sham control group, with stratification by age and gender to balance baseline characteristics between groups. The randomization sequence will be generated by an independent third-party biostatistician using SPSS 26.0, with group allocation sealed in sequentially numbered, opaque envelopes for strict allocation concealment. After baseline assessment, a dedicated study coordinator (fully blinded to group assignment) will open envelopes in numerical order to assign eligible participants.

Given the anatomical specificity of active and sham stimulation sites, intervention staff responsible for electrode placement and device operation cannot be blinded to group allocation. To mitigate potential bias, we have implemented pre-specified rigorous safeguards: The blinded coordinator exclusively manages group allocation, and only provides intervention staff with pre-marked anatomical diagrams of stimulation sites, with no disclosure of group identity at any time. Non-blinded intervention staff are strictly barred from outcome assessment, data entry, statistical analysis, or any communication with participants about group allocation or expected intervention effects. Both groups use identical stimulators with consistent nominal parameters; all intervention staff receive centralized standardized training to ensure identical operational execution and participant interaction across groups.

All outcome assessors, data analysts, biostatisticians, and participants will remain fully blinded to group allocation throughout the trial. Furthermore, treating physicians are solely responsible for routine clinical management and safety assessments; they have no access to group allocation and are strictly isolated from intervention implementation and outcome assessment. Participants will be informed that both interventions may induce a mild tingling sensation, and subjective feeling cannot be used to infer group assignment, to minimize anticipation bias. Outcome assessors will receive standardized training and regular inter-rater reliability checks to reduce measurement bias.

The effectiveness of the blinding will be formally assessed in Weeks 2 and 4 using the validated James Blinding Index (BI) method (James et al., 1996). The detailed statistical procedures for this assessment are outlined in the “Statistical Methods” section.

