**Figure 2 F2:**
[figure not shown]
Device and stimulation sites. Both groups used the HuaTuo SDZ-IIB device with identical parameters. Red dots indicate taVNS sites: CO7 (large intestine point) and CO13 (spleen point) in the cymba conchae. Blue dots indicate sham sites: SF2 (wrist point) and SF4 (shoulder point) in the scapha.

Stimulation site: auricular regions with high density of auricular branch vagus nerve (ABVN) fibers—specifically the cymba conchae and cavum conchae—targeting auricular “Large Intestine Point” (CO7) and “Spleen Point” (CO13) points as anatomical targets for modulation of gastrointestinal function.

Preparation: prior to each stimulation session, trained personnel will disinfect the skin, place and secure electrodes over the marked sites, and verify electrode impedance and device function.

Stimulation parameters: intermittent stimulation with an on/off cycle of 2 s on/3 s off; pulse width of 0.5 ms; frequency approximately 25 Hz; and current intensity individualized within the range 0.5–1.5 mA, titrated to achieve a mild tingling or warm sensation without pain. Intensity will be adjusted according to participant tolerance. This treatment protocol is based on a multicenter randomized controlled trial protocol validated for gastrointestinal disorders (Zhu et al., 2021; Shi et al., 2024; Yin, 2025). Furthermore, evidence from Molefi et al. (2025), which examined healthy subjects with visual-induced motion sickness and found that a 20 Hz frequency combined with a 0.2 ms pulse width did not significantly improve the composite gastrointestinal symptom score, further supporting the rationale for our choice of parameters.

Adverse sensations: if a participant experiences notable discomfort during stimulation, the intensity will be reduced or the session terminated and the event recorded as an adverse event (AE).

Detailed session duration and scheduling will follow the study protocol (see Figure 2 and the procedure manual), and all interventions will be administered by personnel trained in taVNS application.

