#### Control arm (sham)

2.6.3

The control arm will receive a sham stimulation designed to control for non-specific effects of device application and patient interaction while avoiding stimulation of vagal auricular sites. Procedures mirror those of the intervention arm with the following distinctions:

Stimulation site: electrodes will be placed on the scapha (non-vagal area), targeting auricular “Shoulder Point” (SF4) and “Wrist Point” (SF2) points that are not anatomically associated with ABVN or gastrointestinal vagal pathways, ensuring no anatomical overlap with the active taVNS targets (Peuker and Filler, 2002).

Device and procedures: the identical Huatuo SDZ-IIB device model, electrode preparation, disinfection, participant positioning, and nominal stimulation parameter settings (pulse pattern, frequency, and nominal current range) will be used to preserve blinding. The only intentional difference is the stimulation target (site); internal device output routing will be arranged so that the sham site receives a non-vagal stimulation pattern while maintaining similar sensation characteristics.

This sham control procedure is intended to preserve participant blinding and to isolate the specific effects of auricular vagal stimulation.

Notes on safety and documentation.

All interventions, device settings, session timing, and any deviations will be documented in the case report form (CRF). Adverse events will be recorded and managed according to the protocol's safety monitoring plan and reported to the DMC and ethics committee per predefined timelines.

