### Ethics and dissemination

2.12

The study protocol has been approved by the Ethics Committee of Wangjing Hospital, China Academy of Chinese Medical Sciences (Approval No.: WIEC-YJS-2025-003-P002). This trial has been registered in the International Traditional Medicine Clinical Trial Registry (Registration No.: ITMCTR2025001086) prior to participant enrollment, in full compliance with ICMJE requirements for clinical trial registration.

Written informed consent will be obtained from all participants by trained coordinators, including study purpose, procedures, potential benefits/risks, confidentiality, and withdrawal rights.

All AEs/SAEs must be reported within 24 h. The DMC will review safety data and may recommend trial suspension or termination. Results will be disseminated via peer-reviewed journals and conferences using de-identified or aggregated data. Individual data or biosample sharing requires prior Ethics Committee and DMC approval under a data/sample use agreement. Participants will receive a plain-language summary, and key points will be posted on the hospital website.

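### The coordinator who opens the allocation envelopes and hands out the arm-specific site diagrams is called fully blinded, so the bar on unblinded staff does not cover this role

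*Protocol article*

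**What the plan says.** All of the key text is in section 2.5 (Randomization and blinding) of the protocol article. The sequence is generated by an independent biostatistician, and the concealment method is given as "group allocation sealed in sequentially numbered, opaque envelopes for strict allocation concealment". The envelopes come into use once a participant's baseline measurements are complete, when "a dedicated study coordinator (fully blinded to group assignment) will open envelopes in numerical order to assign eligible participants".

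The section then accepts that the staff who place electrodes cannot be blinded, because the active and sham sites differ anatomically. As a safeguard it adds: "The blinded coordinator exclusively manages group allocation, and only provides intervention staff with pre-marked anatomical diagrams of stimulation sites", and says that group identity is never disclosed in doing so. A further safeguard reads "Non-blinded intervention staff are strictly barred from outcome assessment, data entry, statistical analysis", and also covers talking with participants about allocation or expected effects.

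Outcome assessors, data analysts, biostatisticians and participants are said to stay blinded throughout, and treating physicians to have no access to allocation. The coordinator is in neither list.

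The legend of Figure 2 gives the sites. For the active arm it reads "Red dots indicate taVNS sites: CO7 (large intestine point) and CO13 (spleen point) in the cymba conchae"; the corresponding entry for the control arm is "Blue dots indicate sham sites: SF2 (wrist point) and SF4 (shoulder point) in the scapha". Section 2.6.3 (Control arm) says that the target site is the only intended difference between the arms. Section 2.12 states: "Written informed consent will be obtained from all participants by trained coordinators".

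**The concern.** A person who opens an envelope containing the allocation, and then passes on a diagram that differs by arm, knows the arm. Calling that person blinded is more than a loose label, because the label decides who is covered by the protocol's main protection against unblinded staff. That protection is addressed to intervention staff who are not blinded. The coordinator is not intervention staff and is not classed as unblinded, so as written the role is free of the bar.

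The primary outcome is a self-reported symptom score, and the trial relies on separation of duties to protect it. If someone who knows the allocation could enter data or be in contact with participants, that separation would be weaker than the protocol claims. Readers would not know it either, since the limitations paragraph of the Discussion names only the intervention administrators as unblinded. The planned James blinding index (section 2.10) covers participants and outcome assessors, so it would not bring this role to light.

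**Working it through.** No formula applies to the main point. The check sets the statements side by side.

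1. **What the envelope reveals.** Section 2.5 says that the envelopes hold the group allocation. It describes no coded arms (such as A/B) and no sealed diagrams passed on unopened. Opening an envelope therefore shows the arm.
2. **What the diagram reveals.** Active sites are CO7 and CO13; sham sites are SF2 and SF4 (Figure 2 legend). The two sets do not overlap, and site is the only intended difference (section 2.6.3). A diagram marked with the sites identifies the arm.
3. **The protocol's own standard.** Section 2.5 holds that staff working with the sites cannot be blinded, because of the sites. By the same reasoning, the person supplying the marked diagrams cannot be blinded.
4. **How many allocations.** Section 2.4 sets 30 + 30 = 60 participants. One coordinator opens the envelopes in order, so that person knows 60 of 60 if the target is met.
5. **Who is restricted.**

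| Role | Knows the arm? | Status given | Restriction stated |
|---|---|---|---|
| Intervention staff | Yes, from the site | Not blinded | Barred from assessment, data entry, analysis, talk about allocation |
| Allocation coordinator | Yes, from envelope and diagram | Fully blinded | Not named in the bar |
| Assessors, analysts, biostatisticians | No | Blinded throughout | Must stay blinded |
| Treating physicians | No access | No access to allocation | Kept apart from intervention and outcome assessment |

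6. **What is left open.** Someone who has opened the envelopes cannot meet the requirement that assessors and analysts stay blinded, so those tasks are closed to the coordinator in substance. Data entry is not closed: section 2.10 assigns it to two independent researchers and states no blinding for them. Participant contact is not closed either: consent is taken by unspecified coordinators (section 2.12), and the weekly log review by telephone or remote platform is done by unspecified study staff (section 2.6.4).
7. **A second inconsistency.** The same paragraph says that intervention staff cannot be blinded and that they receive the diagrams with group identity never disclosed. Both can hold only if the second means that the arm is not named aloud, which is not what it says.

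**The case against.** The label might mean blinded until each envelope is opened. That could fit its first use, but the protocol still calls the coordinator blinded at the later step of handing out diagrams, so this reading does not rescue the text.

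A stronger defence is that the role may be confined to allocation. The coordinator is described as dedicated and as exclusively managing allocation, and the Discussion refers to strict segregation of duties. If this person does nothing else, the false label does no harm. The wording can equally mean that nobody else manages allocation, so the defence is plausible but not secured. It does stand to this extent: no section gives this coordinator outcome assessment, data entry, consent, enrolment or telephone calls.

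Several stronger conclusions are tempting and should not be drawn:

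- **Weakened concealment at enrolment.** A reader might infer that the coordinators who take consent in section 2.12 include this one, who would then know earlier allocations when enrolling the next participant. The documents do not say so. Section 2.2 gives screening to the study team, and envelopes are opened only after baseline assessment.
- **A share of predictable assignments.** A reader might work one out by assuming permuted blocks. The article mentions no blocks and no block size, the randomization is stratified by age and gender, and nothing says that the coordinator enrols. No such figure can be derived.
- **Bias through the staff section of the symptom score.** That part of Table 2 records a total, a category from fixed cut-offs, the patient's own rating and whether the two agree. It is clerical scoring of self-report, and it is not assigned to the coordinator.

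Detailed delegation of tasks may sit in the full protocol or operating procedures, and its absence from the article is not the point. The point is a statement in the article that cannot be true.

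**Conclusion.** The point holds as an inconsistency in section 2.5 with a practical consequence. The blinding claimed for the allocation coordinator cannot exist once an envelope is opened, and because of the label the bar on unblinded staff does not reach this role. The remaining gap is data entry and participant contact; outcome assessment and analysis are closed indirectly by the rule that those roles stay blinded.

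The size is one person with knowledge of up to all 60 allocations, outside the written bar. This assumes that the envelopes show the arm in clear, as the text says, and that the diagrams reach the coordinator unsealed, since no sealing is described. The documents support no estimate of bias in the score and no claim that a breach occurred. It should be corrected because the remedy is small and the procedure may be carried into the confirmatory trial that this pilot is meant to inform.

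**What to change.** In section 2.5:

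- Describe the coordinator as unblinded from envelope opening onward, and drop the blinded label in both places.
- Name the coordinator in the existing bar on outcome assessment, data entry, statistical analysis and communication with participants about allocation or expected effects.
- State that this person does not obtain consent, enrol participants, make log-review calls or collect the blinding questionnaires.
- Keep the non-disclosure instruction but reword it: the arm is not named to intervention staff or participants, while operators can infer it from the site. Removing it altogether would lose a useful instruction.

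In the limitations paragraph of the Discussion, list the coordinator with the intervention administrators as an unblinded role.

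The cost is a few sentences. If the coordinator in practice has any of the excluded tasks, they must pass to someone else. The documents give no staff numbers, so whether this needs another person cannot be judged from them. Design, sample size and data collection do not change.

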### Interventions

2.6

This is a parallel-group trial employing a “standard care + targeted intervention” design. Both groups will receive standardized diabetes management and metformin therapy as background treatment; in addition, participants will receive either taVNS or sham control group. The treatment course for both arms is 2 weeks, with subsequent follow-up assessments.

#### Standard care (background therapy)

2.6.1

Background therapy follows international guideline recommendations and comprises standardized lifestyle counseling and medication management. Lifestyle counseling includes: dietary guidance with carbohydrates accounting for 45–60% of total daily energy intake and dietary fiber ≥25 g/day; at least 150 min/week of moderate-intensity aerobic activity (for example, brisk walking or cycling); and standardized education on disease management, medication adherence, and management of gastrointestinal symptoms to ensure consistency across participants (American Diabetes Association, 2024a,b).

Medication management principles are as follows:

Discontinue or avoid medications known to exacerbate gastrointestinal symptoms where clinically appropriate (e.g., stimulant laxatives or certain over-the-counter preparations);

In participants with inadequate glycaemic control, additional antihyperglycaemic agents (for example, SGLT2 inhibitors or DPP-4 inhibitors) may be added as clinically indicated, provided such additions are unlikely to aggravate gastrointestinal function; adjustments will follow current guideline recommendations and be documented;

Concomitant treatment for chronic conditions (e.g., antihypertensives for hypertension or secondary prevention therapies for coronary artery disease) will be maintained but clinicians should avoid introducing agents known to provoke GI intolerance when alternatives are available.

Metformin dosing will follow a “start low, escalate gradually” regimen: initial dose 500 mg administered with meals twice daily; dose titration will proceed weekly guided by fasting blood glucose (target 4.4–7.0 mmol/L), with a maximum dose up to 2,000 mg/day or the participant's maximal tolerated dose. Dose adjustments and all concomitant medications will be supervised and recorded by study physicians. In the event of severe, poorly tolerated diarrhea (e.g., ≥5 bowel motions per day with clinical signs of dehydration), metformin will be withheld or adjusted and symptomatic therapy provided (e.g., diosmectite); severe events will be managed according to the study Serious Adverse Event (SAE)—defined per the Common Terminology Criteria for Adverse Events (CTCAE) as any adverse event resulting in death, life-threatening illness, hospitalization, persistent disability, or requiring immediate emergency intervention—procedure and continue to be followed up (Rena et al., 2013).

To ensure ethical fairness, control-group participants who meet predefined criteria at study end may be offered compensatory taVNS treatment if clinically appropriate; this arrangement will be described in the informed consent form.

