### Recruitment

2.2

Participants will be recruited from the outpatient clinics of Wangjing Hospital, China Academy of Chinese Medical Sciences, via hospital posters, internal notices and the hospital's official WeChat account. The study team will screen potential participants against the predefined inclusion and exclusion criteria. Only individuals who meet all eligibility criteria and who provide written informed consent will be enrolled. All study data will be managed by authorized personnel; access will be restricted to designated, authorized members of the study team and the independent DMC. Personally identifiable information will be kept strictly confidential and stored in encrypted form in accordance with applicable institutional and national data-protection regulations.

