#### Treatment schedule and operational management

2.6.4

All participants will receive two stimulation sessions per day (morning and evening), each lasting 30 min, on 5 consecutive weekdays (Monday–Friday) for 2 consecutive weeks (total 10 sessions). During the initial treatment phase, the first three sessions will be administered and supervised in hospital outpatient or inpatient settings by trained study personnel; these sessions also serve as hands-on training for participants who will continue treatment at home. Thereafter, participants may complete remaining sessions at home according to the training protocol.

Home-based treatment requires daily completion of a treatment log documenting treatment time, device current intensity, local sensations, and any gastrointestinal symptoms. Study staff will review logs and confirm adherence weekly by telephone or via a secure remote platform, and will address participant queries. All interventions and any medication adjustments will be performed according to standard operating procedures (SOPs), recorded contemporaneously, and entered into the case report form (CRF).

Any deviation from the prescribed stimulation parameters or protocol procedures must be recorded with rationale. All staff administering or supervising treatments will be trained and certified according to the study training curriculum; competency assessments will be documented.

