#### Recording and reporting of adverse events

2.8.1

All AEs and serious adverse events (SAEs) must be thoroughly documented in case report forms (CRF/eCRF), including event name, onset/offset dates, severity, interventions, clinical outcome, and investigator-assessed causality with study intervention. Investigators should provide prompt treatment upon identification of an AE and complete initial documentation. SAEs must be reported to the principal investigator and sponsor within 24 h and submitted to the ethics committee and regulatory authorities as required. Subjects who discontinue due to AEs should be followed until resolution, and outcomes recorded.

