### Safety evaluation

2.9

All AEs will be graded and analyzed according to standardized systems. For practical purposes, a simplified grading mapped to the CTCAE is applied as follows:

Grade 1 (Mild): Minor symptoms requiring no intervention or only simple supportive care.

Grade 2 (Moderate): Requires outpatient management or limitation of daily activities.

Grade 3 (Severe): Requires hospitalization or prolongation of hospitalization.

Grade 4 (Life-threatening): Requires emergency intervention or life support.

Grade 5: Death directly related to the AE.

Safety endpoints include incidence, severity distribution, onset timing, intervention-related causality of AE/SAE, and laboratory abnormalities (CBC, liver and renal function). Results are primarily descriptive, with between-group comparisons performed as appropriate. De-identified individual case information may be disclosed.

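### The stated SAE definition omits prolongation of hospitalization, which the grading scale names for Grade 3, so an event that only lengthens a stay is severe but, read literally, not an SAE (minor)

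*Protocol article*

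**What the plan says.** The article's only SAE definition is an aside in section 2.6.1 (Standard care), inside a sentence on severe diarrhea under metformin. It covers "any adverse event resulting in death, life-threatening illness, hospitalization, persistent disability, or requiring immediate emergency intervention".

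Section 2.9 (Safety evaluation) sets the severity scale: "Grade 3 (Severe): Requires hospitalization or prolongation of hospitalization". It also makes the incidence and severity distribution of AEs and SAEs safety endpoints, analysed mainly descriptively.

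Section 2.8.1 requires every AE and SAE to be documented with its severity and outcome. It then sets a rule for SAEs alone: "SAEs must be reported to the principal investigator and sponsor within 24 h", with onward submission to the ethics committee and regulators as required.

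Two other sentences cover adverse events generally. The safety notes at the end of 2.6.3 send them to the DMC and ethics committee on predefined timelines, and 2.12 applies a 24-hour limit to AEs and SAEs alike.

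On setting, 2.2 states "Participants will be recruited from the outpatient clinics of Wangjing Hospital", while 2.6.4 states that "the first three sessions will be administered and supervised in hospital outpatient or inpatient settings by trained study personnel".

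**The concern.** The SAE definition and the grading scale describe hospital-related events differently. An event that causes an admission is both Grade 3 and an SAE. One that extends an admission already under way is Grade 3, but matches nothing on the SAE list. Two events of the same grade would then be classified differently only because of where the participant was at onset.

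SAE status has consequences. It decides whether an event enters the SAE count, and whether the explicit route in 2.8.1 to the principal investigator, sponsor and regulators applies. In arms of 30, a single SAE is visible in the results.

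**Working it through.** No figure in the plan depends on this wording, so the check sets the sections side by side.

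**1. Is the definition open or closed?** Section 2.6.1 gives five criteria: death, life-threatening illness, hospitalization, persistent disability, and need for immediate emergency intervention. There is no catch-all and no indication that these are examples. Prolongation is absent.

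**2. Does hospitalization already include a prolonged stay?** Section 2.9 joins the two with an or: "Requires hospitalization or prolongation of hospitalization". If the first term covered the second, the second would be redundant. The document's own usage therefore favours reading them as different events, though it does not prove it.

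**3. Classification on the literal reading.**

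| Event | Grade (2.9) | SAE (2.6.1) |
|---|---|---|
| Causes an admission | 3 | Yes |
| Only prolongs an existing stay | 3 | No |

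**4. What happens to the second kind of event?**

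| Step | Section | Applies? |
|---|---|---|
| Documented with severity and outcome | 2.8.1 | Yes, all AEs |
| Tabulated as a Grade 3 AE | 2.9 | Yes |
| Sent to the DMC and ethics committee | 2.6.3 | Yes, adverse events generally |
| Covered by a 24-hour limit | 2.12 | Yes, AEs and SAEs; no recipient named |
| Explicit 24-hour report to principal investigator and sponsor | 2.8.1 | Not clearly; tied to SAEs |
| Regulatory submission | 2.8.1 | Not clearly; tied to SAEs |
| Included in the SAE count | 2.9 with 2.6.1 | No |

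**5. Size per event.** Section 2.4 plans 30 participants per group. One participant whose only such event is left unclassified changes that arm's SAE incidence by 1/30 = 0.033, or 3.3 percentage points.

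**6. How often could it arise?** The article gives no number of inpatients, so no expected count can be derived. Recruitment is from outpatient clinics. Only the first three sessions are supervised in hospital; at two sessions a day these span about two days. A participant admitted during the study for an unrelated reason could also have a stay prolonged by an adverse event.

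**The case against.** A reader might infer that a stay-prolonging event escapes safety capture or goes unreported. The article does not support that. The documentation rule in 2.8.1, the DMC and ethics committee route in 2.6.3 and the general limit in 2.12 all apply without SAE status, and the event still appears in the severity table. This part of the objection stands and confines the point to the SAE label and count and to the sponsor and regulator route in 2.8.1.

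It can also be said that 2.6.1 itself supplies a bridge, since "severe events will be managed according to the study Serious Adverse Event (SAE" (the sentence goes on to the procedure) and Grade 3 is labelled Severe. That helps for severe diarrhea under metformin, the subject of that sentence. Read more widely, it would route every Grade 3 event into a procedure whose definition, in the same sentence, leaves some of them out. It does not settle classification.

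Exposure is plausibly close to nil. The gap needs someone already in hospital for a reason other than an adverse event, whose stay is lengthened by an event meeting none of the five criteria. The phrase "hospital outpatient or inpatient settings" may describe only where sessions are held, and nothing says that admitted patients will be enrolled. This stands as a reason for low severity.

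Finally, the article condenses a fuller protocol, and the safety monitoring plan and SOPs it mentions are not shown; they may hold a complete definition. That limits what can be said about the trial as run. It does not remove the mismatch, because the article states a definition and that definition does not fit its own grading scale.

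**Conclusion.** The point holds as a minor inconsistency. Followed literally, the SAE definition in 2.6.1 leaves out a type of event that 2.9 grades as severe. Such an event is not counted as an SAE, and the explicit principal investigator, sponsor and regulatory route in 2.8.1 does not clearly reach it. Section 2.12 has a wider 24-hour scope than 2.8.1, so the two reporting rules also need to be reconciled.

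The size is 3.3 percentage points of SAE incidence in one arm per affected participant, with 30 per arm as the denominator. The number of affected participants cannot be estimated from the article and is probably small. The figure is therefore not an estimate of bias in the SAE comparison.

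The conclusion assumes that the list in 2.6.1 is exhaustive and that hospitalization there does not include a prolonged stay. The wording of 2.9 supports the second assumption without proving it. If hospitalization was meant to include prolongation, only a clarification is needed.

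**What to change.** Add prolongation of existing hospitalization to the SAE definition and state the full definition in 2.8.1, where SAE reporting is set. Section 2.6.1 can then refer to it. Reconcile 2.6.1, 2.8.1, 2.9 and 2.12 so that they share one SAE wording and one reporting rule, including which events the 24-hour limit covers and who receives the report. Check that the SAE form, the safety monitoring plan and the SOPs carry the same text.

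The cost is one phrase, a relocated definition and a check of the form. Sample size, analysis model and treatment are unaffected. The reported SAE count could rise slightly.
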